#### *ACT processes*

The Distress Tolerance Scale (DTS). This measures ability to tolerate distress.

The Philadelphia Mindfulness Scale (PHLMS). This measures present moment awareness and acceptance.

The Drexel Defusion Scale (DDS). This measures cognitive distancing or 'defusion'.

The Physical Activity Acceptance Questionnaire (PAAQ). This measures the extent to which an individual is able to tolerate physical or psychological discomfort.

The Food Acceptance and Awareness Questionnaire (FAAQ). This measures acceptance of food-related thoughts and urges.

#### *Tertiary qualitative outcomes*

A nested qualitative, semi-structured interview study will be conducted with 12 participants (six ACT; six control) following the 12 month follow-up in order to understand the 'what, why and how come' of participants' beliefs and behaviours in order to inform the design and delivery of a future full RCT. A topic guide will prompt participants to discuss their experience of participation in the study and in the groups. The topic guide will be informed by the study and intervention processes, observations made by the study team, study psychologist, Usual Care Support Group co-ordinator and participants during the groups. It will be developed with service user advisors and will take approximately 1 hour to complete. Interviews will be recorded and transcribed verbatim.

#### *Statistical data analysis*

Analyses will be undertaken using R program. All significance tests will be 2-tailed and alpha will be set at  $p < 0.05$ . The distribution of the study population will be characterised using descriptive summary statistic parameters, that is median, range, mean, and standard deviation. Then, we propose to use ANCOVA to calculate variations within primary and secondary outcome measures pre-treatment and at follow-up. Anonymised data from those who decline to participate will also be reported. Complete case analysis and intent-to-treat analyses (using last measurement carried forward for participants who provided baseline assessment measurements) will be conducted.

A cost-consequence analysis (CCA) will be carried out from a National Health Service (NHS) perspective. This involves listing the costs and outcomes associated with ACT and the Usual Care Support Group separately, allowing decision-makers to compare the relative value of approaches, and by calculating resource use. The intervention costs will be calculated based on the activities involved in delivering the programme such as staff salaries, administrative and managerial costs.

Total costs of the individuals in the two groups will be compared and estimated by multiplying the resource use with the unit costs of health and social care. We will present the additional costs associated with the intervention and present the costs alongside the benefits (if any) identified in the trial. Sensitivity analyses to model uncertainties around all key cost and outcome parameters, and plausible ranges will be specified using information from the trial and from the literature specific to the population in the study will be conducted.

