### **Sample size**

As this is a feasibility study and no hypothesis testing will occur, a power calculation has not been conducted. Sample sizes between 24 and 50 have been recommended for feasibility studies, however to allow for loss to follow up, estimated at 30%, we will aim to recruit 58 participants. Loss to follow up and intervention and Usual Care Support Group attrition, including reasons, will be recorded to inform power calculations for a definitive RCT. This information will be recorded in a consort diagram.

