**Data collection and measures**

A standardised battery of measures will be completed at baseline, three, six and 12 month follow up, except for weight and the King’s Obesity Staging Criteria which will be collected at baseline and 12 month follow up only to allow for meaningful change. Demographic data: self-reported medical history, age, gender, work status, educational level, ethnicity, marital status, number of dependents, current or past psychological therapy and current medications, will also be collected at baseline. Baseline and 12 month follow up data will be collected face to face to coincide with routine clinic appointments; three and six month follow up data will be collected via telephone.

*Primary outcome measures*

The primary outcome is the feasibility of the trial methodology. This will be measured by, (1) The willingness of participants to be randomised, measured by recording the number of participants who drop out of the study after they have been randomised, (2) the number of eligible patients attending clinic, as assessed by calculating the percentage of patients who meet eligibility criteria at screening, (3) follow-up rates, assessed by the percentage of participants retained until 12 month follow-up and providing complete datasets, (4) adherence to the intervention or control, assessed by number of sessions attended, (5) reasons for attrition, (6) the time needed to collect data and (7) the acceptability of the intervention at 12 month follow-up, as assessed by a 5 point likert scale (1=“Not at all”, 3=“somewhat”, 5=“Very”) to evaluate how helpful participants found the treatment, their satisfaction with it, and how likely they would be to recommend it to a friend and (8) the standard deviation of weight maintenance (<5% weight gain from baseline assessment) or weight loss, in order to estimate the required sample size for a future trial (measured at study close-out).

*Secondary outcome measures*

Outcomes relating to (A) obesity, health and wellbeing, (B) costs, and (C) measures of ACT processes will be collected to test the appropriateness and acceptability of measurement instruments to be used as outcomes in a full trial. The validated instruments to be used are listed below.

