## **DISCUSSION**

This study aims to establish the feasibility of conducting a larger scale RCT to examine the impact of ACT on bariatric patients 15-18 months post-surgery. Previous small-scale studies of acceptance-based behavioural intervention for post-operative populations have found benefits in favour of ACT compared with usual care. The different studies focused on different outcomes, but benefits identified included reduced cravings and sweet consumption, reduced disordered eating and improved body dissatisfaction and quality of life, as well as weight loss (a clinically significant average of 6 kg or 5% weight loss in treatment completers,  $n=23$ ). Enhanced psychological flexibility, a core ACT process, was identified as one mediator for benefits in one trial, though other processes have also been proposed as important. This study will therefore examine a wide range of potential treatment outcomes and will test for possible mediators and moderators of effect. In the earlier studies, the time since surgery varied widely between participants. The current study will focus on patients who have reached a critical stage in their treatment; a stage which has been identified as high risk for weight regain and at which point they are currently discharged from services.

Despite the potential benefit of psychological intervention and recommendations within various guidelines that it should be offered to bariatric patients, psychological support is not provided as part of routine post-operative care. Such support could potentially reduce the high costs to the patient and to society of weight regain, re-operations and the return of physical and psychological co-morbidities post bariatric surgery. This feasibility trial is the first step in helping to determine whether ACT group therapy is acceptable to post-bariatric surgery patients, and will provide insight into the optimal methods to employ for a future randomised controlled trial to determine its effectiveness.

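### Carrying the last measurement forward scores every participant without a 12-month weight as zero change and maintained, and the protocol does not say whether this data set supplies the SD for sizing the next trial

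*Protocol*

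**What the plan says.** Under Data collection and measures, the protocol lists a battery repeated at baseline, 3, 6 and 12 months, with an exception for "weight and the King’s Obesity Staging Criteria which will be collected at baseline and 12 month follow up only". In the same section, primary outcome (8) is given as "the standard deviation of weight maintenance (<5% weight gain from baseline assessment) or weight loss, in order to estimate the required sample size"; the sample size meant is that of the later, definitive study.

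Under Statistical data analysis, two analyses appear in one sentence: "Complete case analysis and intent-to-treat analyses". The second is defined by its rule for missing data: "intent-to-treat analyses (using last measurement carried forward for participants who provided baseline assessment measurements) will be conducted". The paragraph applies to primary and secondary outcomes alike. It does not say which of the two analyses supplies the SD in outcome (8).

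Under Sample size, the target is set "to allow for loss to follow up, estimated at 30%, we will aim to recruit 58 participants".

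On timing, "Baseline and 12 month follow up data will be collected face to face to coincide with routine clinic appointments". The Discussion describes recruitment as a stage with a high risk of regain, "at which point they are currently discharged from services".

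**The concern.** For the questionnaires, carrying the last value forward can draw on month 3 or month 6. For weight and King's staging nothing lies between baseline and 12 months, so the rule becomes baseline carried forward. A lost participant receives a change of exactly 0 kg and an unchanged King's stage. Zero change is below the 5% gain limit, so that participant also counts as a success. This conflicts with the protocol's own rationale, which is that people at this stage tend to regain.

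Three results are exposed:

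- The maintenance proportion rises.
- Imputed zeros are counted as observed data, so precision is overstated.
- If the SD for outcome (8) were computed on this set, it could be too small. Giving a usable SD is one of the things the feasibility trial is meant to do.

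**Working it through.** **Inputs.** From the protocol: target 58, loss d = 0.30, two-sided alpha 0.05, equal allocation, weight at two times only. The Introduction cites significant regain in up to 20%, and the Discussion cites a mean loss of 6 kg in completers of earlier work. The protocol gives no SD of weight change, so SD effects are shown as ratios. SDs in kg are assumptions.

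**The protocol's own figure.** 40 / (1 − 0.30) = 57.1, rounded up to 58. The 40 is inferred, but it lies within the 24 to 50 that the protocol cites. Expected loss is 58 × 0.30 = 17.4, leaving 58 × 0.70 = 40.6. The target is not affected by this point.

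**Maintenance rate.** All the lost count as maintained, so p becomes (1 − d)p + d. With p = 0.80: 0.7 × 0.80 + 0.30 = 0.86. Apparent regain falls from 20% to 14%. This takes 80% as the rate in the lost as well; if they regain more often, the gap is wider.

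**SD of change.** Let observed changes have mean μ and SD s. Setting a share d to zero gives variance (1 − d)s² + d(1 − d)μ², so

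SD ratio = √[(1 − d)(1 + d(μ/s)²)].

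This is below 1 only if |μ|/s < 1/√(1 − d), which is 1/√0.70 = 1.195 at d = 0.30.

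**Effect on a later trial.** As an illustration, assume a target difference of 0.5 observed SD and 80% power. Then n per arm = 2(1.96 + 0.84)²(SD/difference)², which is 63 with the observed SD. True power at a smaller n is Φ(0.5√(n/2) − 1.96).

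| Mean change (in SD) | SD ratio at d = 0.30 | n per arm if that SD is used | True power |
|---|---|---|---|
| 0 | 0.837 | 44 | 65% |
| 0.5 | 0.867 | 48 | 69% |
| 0.75 | 0.905 | 52 | 72% |
| 1 | 0.954 | 58 | 77% |

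At 1.2 SD the ratio is 1.001, so there is no reduction.

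**Sensitivity.**

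- Share missing, at mean change zero: the ratio is 0.949 at 10%, 0.894 at 20% and 0.775 at 40%.
- Mean loss of 6 kg with d = 0.30: for assumed SDs of 5, 6, 8, 10 and 12 kg the ratio is 1.001, 0.954, 0.905, 0.881 and 0.867.
- Outcome (8) read as a yes/no variable: at 80% maintained, the SD falls from √(0.80 × 0.20) = 0.400 to √(0.86 × 0.14) = 0.347. It shrinks only if 0.7(0.7p + 0.3) < p, that is p > 0.21/0.51 = 0.41. At 30% maintained, the rate reads 51% and the SD rises from 0.458 to 0.500.

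**Precision.** With 17 of 58 imputed and mean change zero, the sample SD ratio is 0.838. The nominal standard error of mean change is then 0.838 × √(41/58) = 0.70 of that from the 41 observed weights, although no information has been added.

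**The case against.** The strongest reply is that the sentence containing the carry-forward rule also plans a complete case analysis, whose SD contains no imputed zeros. Nothing ties outcome (8) to the carried-forward set, and the SD also appears among the descriptive statistics, ahead of the missing-data sentence. A reader might infer that the protocol commits the next trial to a deflated SD. The text does not support that. It leaves the source open.

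The size is also conditional. The 0.84 ratio and 65% power need 30% of 12-month weights missing and a mean change near zero. The 30% is an estimate of overall loss, and the share without a 12-month weight may differ. The power figures further assume that a planner takes the carried-forward SD despite having complete-case results, and sets the target difference independently of that data set. These limits stand.

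A reader might also infer from the discharge statement that more than 30% of weights will be missing. That does not follow. The Introduction says that patients are approaching discharge and may be discharged at this stage, and the protocol does plan face-to-face collection at 12 months. The two statements are in tension, but no rate can be drawn from them.

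Finally, this is a feasibility study that disclaims hypothesis testing, and a SAP could settle the analysis set. That lowers the severity. It does not rescue the rule: the protocol itself fixes both the imputation method and the weight schedule, and together they give a wrong result.

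**Conclusion.** The point holds in a conditional form. The direct defect is certain whenever a 12-month value is missing: the intent-to-treat analysis scores that participant as unchanged in weight and King's stage, and as maintained. At 30% missing, 80% maintenance reads 86%, and precision is overstated.

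The effect on the next trial is an open risk, because the protocol does not name the source of the sizing SD. If the carried-forward set were used at 30% missing, the SD of change would be 0.84 to 0.95 of the observed SD for mean changes of 0 to 1 SD. True power would be about 65% to 77% against a planned 80%. There would be no reduction at about 1.2 SD. The power figures do not depend on the kg value of the SD, but they do rest on the assumed 0.5 SD difference and normal-approximation formulas. This should be fixed before analysis, but it does not undermine the feasibility design.

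**What to change.** 1. State that the SD of weight change, with its confidence interval, and the maintenance proportion come from observed 12-month weights, and report the number observed.
2. Drop carry-forward for weight and King's staging. For between-arm weight estimates, use baseline-adjusted ANCOVA on observed data or with multiple imputation. With about 40 observed weights, imputation adds little unless useful auxiliary variables exist. Neither approach protects against loss that depends on unseen regain, so a sensitivity analysis for that is a reasonable option.
3. For the questionnaires measured at 3, 6 and 12 months, use a likelihood-based mixed model.
4. Separately, reconcile the plan to collect 12-month data at routine clinic appointments with the Discussion's statement that patients are discharged at this stage, so that it is clear how the weight is obtained.

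The cost is a few sentences and a little more programming. The downside is small: somewhat more analysis work, and probably a larger SD and hence a larger definitive trial. The recruitment target of 58 does not change.

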### *Obesity and health and wellbeing*

The King's Obesity Staging Criteria. This measures the severity of an individual's obesity based on a four-graded set of health-related domains. It can capture health problems related to obesity and health benefits after weight loss.

The International Physical Activity Questionnaire (IPAQ). This measures levels of physical activity.

The Brief Mediterranean Diet Questionnaire. This measures adherence to a Mediterranean diet which is recommended as part of the intervention.

The Alcohol Use Disorders Identification Test (AUDIT). This measures alcohol consumption, drinking behaviours, and alcohol-related problems.

The Dutch Eating Behaviour Questionnaire (DEBQ). This measures eating behaviour in terms of restraint, emotional, and external eating.

The Hospital Anxiety and Depression Scale (HADS). This measures levels of anxiety and depression.

Weight in kilograms.

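### Costs are to be set beside whichever benefits are identified, with p<0.05 the only stated criterion, although the protocol elsewhere rules out hypothesis testing

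*Protocol*

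**What the plan says.** The Statistical data analysis section of the protocol gives one rule for inference: "All significance tests will be 2-tailed and alpha will be set at" p<0.05. It continues: "we propose to use ANCOVA to calculate variations within primary and secondary outcome measures pre-treatment and at follow-up". No secondary outcome and no follow-up visit is singled out. Each analysis is to be done twice, on complete cases and with the last measurement carried forward.

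The same section describes the cost-consequence analysis as setting out costs and outcomes for ACT and for the support group separately, so that decision-makers can weigh one approach against the other. It then says the trial will "present the costs alongside the benefits (if any) identified in the trial".

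On what is measured, Data collection and measures states: "Outcomes relating to (A) obesity, health and wellbeing, (B) costs, and (C) measures of ACT processes will be collected". The purpose given there is to see whether the instruments are suitable and acceptable for a full trial. On timing: "A standardised battery of measures will be completed at baseline, three, six and 12 month follow up". Weight and the King's Obesity Staging Criteria are the exceptions, "which will be collected at baseline and 12 month follow up only to allow for meaningful change".

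The Sample size section says that, this being a feasibility study, there will be no hypothesis testing and hence no power calculation. The Discussion nevertheless says: "This study will therefore examine a wide range of potential treatment outcomes and will test for possible mediators and moderators of effect".

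**The concern.** The protocol is inconsistent about what the secondary outcomes are for. Two sections treat the trial as one that tests no hypotheses and tries out instruments. The analysis section sets a significance level for all tests, applies ANCOVA to the secondary measures and speaks of benefits being identified.

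The cost-consequence wording is where this could do harm. A list of outcomes by arm is neutral. A list of identified benefits depends on the results, and the only yardstick the protocol offers for identifying one is p<0.05. With many scores and several visits, that yardstick will often be met by chance in a trial with about 20 completers per arm. A chance finding could then stand beside ACT's extra cost while null or unfavourable outcomes drop out of view, in a table meant to help decision-makers compare the two approaches.

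**Working it through.** **Retained sample.** Sample size gives 58 recruited and 30% loss: 58 × 0.70 = 40.6, so about 20 per arm. The protocol cites a recommended range of 24 to 50; 24/0.70 = 34.3 and 50/0.70 = 71.4, which round up to 35 and 72, so 58 is consistent with it. The protocol states no number of tests and no overall error rate, so there is no figure of its own to reproduce on this point.

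**Number of tests.** Fourteen secondary instruments are listed, leaving out the CSRI, which supplies the cost data:
- seven on obesity, health and wellbeing: King's staging, IPAQ, Mediterranean diet, AUDIT, DEBQ, HADS, weight;
- two under costs: EQ-5D-5L, ICECAP-A;
- five on ACT processes: DTS, PHLMS, DDS, PAAQ, FAAQ.

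Twelve have three post-baseline visits and two have one.
- 12 months only, one score per instrument: 14 tests.
- 12 months only, with the scales the protocol names: DEBQ three ("This measures eating behaviour in terms of restraint, emotional, and external eating"), HADS two, PHLMS two. This adds 2 + 1 + 1 = 4, giving 18 tests.
- All visits, one score each: 12 × 3 + 2 = 38.
- All visits, named scales: 16 × 3 + 2 = 50.

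The second analysis set and the mediator and moderator tests are not counted.

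**Chance of a false result favouring ACT.** A two-sided 0.05 test puts 0.025 in the favourable direction. With m independent tests and no true effect, the chance of at least one is 1 − 0.975^m, and the expected number is 0.025m. The expected number does not depend on correlation.

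| Tests (m) | At least one favouring ACT, independent | Expected number |
|---|---|---|
| 14 | 1 − 0.975^14 = 30% | 0.35 |
| 18 | 1 − 0.975^18 = 37% | 0.45 |
| 38 | 1 − 0.975^38 = 62% | 0.95 |
| 50 | 1 − 0.975^50 = 72% | 1.25 |

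**Allowing for correlation.** The protocol gives no correlations, so these are assumed. The figures come from a simulation with no effect, 20 per arm, 2,000 replicates per setting and two-sided t-tests at 0.05 standing in for baseline-adjusted ANCOVA.

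| Correlation between instruments / between visits | 38 tests | 50 tests |
|---|---|---|
| 0.3 / 0.5 | 44% | 52% |
| 0.5 / 0.7 | 31% | 33% |

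For 12 months only, a between-instrument correlation of 0.3 gives 23% (14 tests) and 28% (18 tests); 0.5 gives 19% and 21%. A single test gives 2.5%.

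**Either direction, for comparison.** Independent tests give 1 − 0.95^38 = 86% and 1 − 0.95^50 = 92%. At correlations 0.5/0.7 these fall to 59% and 66%. At 12 months only they are 51% and 60% if independent, and 37% and 39% at correlation 0.5.

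**The case against.** The strongest reply is that the protocol never ties the word identified to a p-value. The cost-consequence text does not mention significance, describes the analysis as covering the outcomes of both arms, and adds sensitivity analyses on the key outcome parameters. On that reading the costs would simply stand beside all the outcomes, and the qualifier in brackets is neutral. This stands in part: the link to p<0.05 is an inference, and selective listing is something the wording permits, not something it prescribes.

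Three stronger readings are tempting and should be resisted.
- A reader might infer that, with no effect, the trial would find a difference about 70-90% of the time. That counts differences in either direction, whereas the sentence is about benefits. It also needs a between-arm test at every visit and low to moderate correlation. The protocol says only that ANCOVA covers measures before treatment and at follow-up.
- A reader might infer that null outcomes will be dropped, or that instruments for the full trial will be chosen by p-value. Neither is stated.
- A reader might infer that a multiplicity correction has been omitted. Such a rule, like the choice of visit and the scoring of subscales, may sit in a statistical analysis plan that is not at hand.

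What remains does not rest on silence. The flat 0.05, the exclusion of hypothesis testing and the results-dependent cost sentence are all in the protocol and do not fit together. A multiplicity rule elsewhere would not mend the cost sentence.

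**Conclusion.** The point holds as an inconsistency that leaves a route to selective reporting. The protocol disclaims hypothesis testing, then sets 0.05 for all tests and places costs beside benefits identified by a criterion it does not define.

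If p<0.05 were that criterion, the chance of at least one false result favouring ACT would be 30-37% with 14-18 independent tests at 12 months (about 19-28% at correlations of 0.3 to 0.5). It would be about 31-72% with 38-50 tests over all visits. These figures illustrate the consequence and are not a property the protocol states. They rest on a between-arm test for each score, on no CSRI test, on subscale scoring for the larger counts, and on assumed correlations. In every scenario examined the chance is far above the 2.5% of a single test.

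**What to change.** Three changes to the text:

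1. Replace the cost sentence with: *present the costs of each arm alongside every secondary outcome listed under Obesity and health and wellbeing, Costs and ACT processes (mean, SD and n per arm, and the baseline-adjusted difference with 95% CI at 12 months), whatever its direction or significance.*
2. Add: *all secondary comparisons are exploratory, and none will be called a benefit of ACT on the basis of p<0.05.*
3. Reconcile the alpha sentence in Statistical data analysis with the exclusion of hypothesis testing in Sample size, so that both say the same about what, if anything, is tested.

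No formal multiplicity correction is asked for; full reporting with intervals suits exploratory measures in a feasibility trial. The cost is a few sentences and a longer table, with no new data and no more participants. The trial gives up naming individual benefits, which a sample of this size was not planned to support.
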